### Intervention

#### Overview

After completing baseline questionnaires, scales, and anthropometric measurements with the assistance of field investigators and dietitians, eligible subjects will be randomly assigned to either the CR diet group or the metformin group in a 1:1 ratio. Participants randomized to the CR diet group will receive standard dietary management, which includes a target energy intake assessment, a pre-intervention education session, and an app-based CR diet program consisting of an 8-week CR phase followed by a 4-week weight maintenance phase. Participants randomized to the metformin group will receive enteric-coated metformin tablets at a total daily dose of 1,500 mg. All participants will be instructed not to alter their physical activity habits throughout the trial to minimize potential confounding factors (45, 46). After the 12-week intervention period, both interventions (CR diet and metformin) will be discontinued, and all participants will undergo OI therapy (up to 5 cycles).

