#### CR diet group

To implement the CR diet, the total energy expenditure (TEE) of each participant will be calculated, and the target daily energy intake will be set at 30–50% below the baseline TEE, depending on the participant’s BMI (47). Before the intervention, the International Physical Activity Questionnaire Short Form (IPAQ-SF), along with weight, height, and age, is used to estimate TEE. The model for calculating TEE is based on basal metabolic rate (BMR) and physical activity level (PAL), as recommended by FAO/WHO/UNU Expert Consultation Report (48, 49):
TEE=BMR∗PAL
(1)

In Equation 1, BMR is calculated using the Mifflin-St Jeor equation (50), which incorporates weight, height, and age, as shown in Equation 2:
$$\begin{array}{c} \mathrm{BMR}=[9.99\times \text{Weight}\;(\mathrm{kg})]+[6.25\times \text{Height}\;(\mathrm{cm})]\\ -[4.92\times \mathrm{Age}\;(\text{years})-161] \end{array}$$
(2)

The PAL value in Equation 1 is determined using IPAQ-SF, which categorizes individuals into activity levels, such as low-level physical activity, moderate-level physical activity, and high-level physical activity (51, 52). The activity levels are then assigned a corresponding PAL, for example, PAL = 1.4 for low-level physical activity, PAL = 1.6 for moderate-level physical activity, and PAL = 1.8 for high-level physical activity (49, 53).

Before the intervention, participants will receive individualized diet plans based on their calculated target energy intake and will be educated on the principles of reducing daily caloric intake. The prescribed macronutrient distribution for each participant will allocate 40–55% of total energy intake to carbohydrates, 15–20% to protein, and 20–30% to fat, aligning with the ranges recommended by current dietary guidelines (54). Participants may select foods according to their usual dietary habits and preferences while adhering to the prescribed energy and macronutrient targets. During dietary counseling, dietitians will consider regional dietary practices, food availability, and affordability to improve the feasibility and adherence to the CR diet. Participants will upload dietary records, and feedback will be provided on whether their macronutrient intake falls within the target ranges to help them maintain the prescribed distribution. In addition, participants will be instructed not to alter their physical activity habits throughout the trial to minimize potential confounding.

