To enhance adherence to the diet intervention in the CR diet group, a custom healthcare service application (app) will be utilized. The app includes two components: a mobile app for participants and an administrator interface for researchers. Through the mobile platform, participants can record food diaries, communicate with dietitians, and receive messages. The dietitians and investigators can access all submitted information and interact with participants via the administrator interface.

Participants will be instructed to record their daily food and beverage consumption using household measures via the app during the 12 weeks of the intervention. Daily uploads including household measurements, photographs, and detailed food descriptions will primarily be used to support dietary adherence through self-monitoring and to provide individualized feedback on the macronutrient distribution. For an objective assessment of actual dietary intake, three 24-h dietary recalls (covering two weekdays and one weekend day) will be extracted by dietitians from participants’ uploaded food diary records. Daily dietary intake will be calculated based on the reported food types and portion sizes, using the nutrient composition data from the Chinese Food Composition Table (55). Adherence to the CR diet will be quantitatively assessed using app-based dietary records through two complementary measures: recording adherence and CR-target adherence. Recording adherence will be calculated as the number of weeks in which a participant records dietary intake on at least 3 days divided by the 12-week intervention period, multiplied by 100%. CR-target adherence will be calculated as the number of weeks in which the participant achieves the prescribed calorie-restriction target divided by the number of weeks meeting the dietary recording criterion, multiplied by 100%. For both measures, adherence will be categorized as high (≥80%), moderate (60–79%), or low (<60%).

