During the first 8 weeks of the intervention, dietitians will provide individualized feedback to each participant twice a week via the app. Feedback will be informed by quantified dietary intake, comprising total energy and the macronutrient distribution (carbohydrates, protein, and fat), derived from participants’ uploaded food-diary records (55). Tailored recommendations regarding adjustments to energy intake and food choices will be subsequently issued by dietitians to ensure adherence to the CR protocol. During the subsequent 4-week weight-maintenance period, dietitians will discontinue active dietary intervention and no longer provided feedback on the CR protocol. However, participants will be required to continue recording their food diaries through the app.

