For the primary outcome, participants who are lost to follow-up and whose live birth status cannot be ascertained will be conservatively classified as not having achieved a live birth. The number and reasons for withdrawal and loss to follow-up will be documented and reported separately for each treatment group. Missing baseline covariate data will be handled using complete-case analysis in the corresponding adjusted models. Multiple imputation will be used in sensitivity analyses to assess the robustness of the results to missing covariate data. Additional sensitivity analyses will be performed to evaluate the potential impact of missing outcome data and loss to follow-up on the primary findings. These analyses will examine alternative assumptions regarding outcomes among participants lost to follow-up and will be compared with the primary analysis in which missing live birth outcomes are classified as no live birth.

Participants with insufficient intervention adherence or protocol deviations will remain included in the primary intention-to-treat analysis according to their randomized treatment assignment. Additional sensitivity analyses will be conducted to assess the potential impact of major protocol deviations on the primary findings. A per-protocol analysis will be conducted as a supportive secondary analysis and will include participants who complete the trial, meet the prespecified intervention-specific adherence criteria, and have no major protocol violations. Primary and secondary outcomes will be compared between treatment groups within the per-protocol population. The per-protocol findings will be interpreted as supportive analyses alongside the primary intention-to-treat results. Secondary outcomes will be compared between groups using a similar approach for categorical variables. Mixed-effects models will be applied for repeated measurements. Exploratory subgroup analyses will be conducted according to prespecified baseline characteristics, including age and BMI. Potential heterogeneity in intervention effects across these characteristics will be assessed by including treatment-by-subgroup interaction terms in the corresponding regression models. Where AMH measurements are available, the potential effect-modifying role of AMH will also be explored in supplementary analyses.

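### CR-target adherence counts recorded weight-maintenance weeks in its denominator, so a woman who follows both diet phases and records all 12 weeks scores 67% and is classed as moderate

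*Protocol article*

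**What the plan says.** The Overview under Intervention describes "an app-based CR diet program consisting of an 8-week CR phase followed by a 4-week weight maintenance phase". The section on the CR diet group sets one energy goal: "the target daily energy intake will be set at 30–50% below the baseline TEE, depending on the participant’s BMI". It gives no separate goal for weeks 9–12. For those last four weeks it says that "dietitians will discontinue active dietary intervention and no longer provided feedback on the CR protocol", while diary entry through the app remains a requirement.

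The same section defines two adherence measures:

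- Recording adherence is "the number of weeks in which a participant records dietary intake on at least 3 days divided by the 12-week intervention period".
- CR-target adherence is the number of weeks in which "the participant achieves the prescribed calorie-restriction target divided by the number of weeks meeting the dietary recording criterion".

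Both are expressed as percentages and classed as high (80% or more), moderate (60–79%) or low (below 60%).

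Under Statistical analysis, the supportive per-protocol set takes in participants who, among other conditions, "meet the prespecified intervention-specific adherence criteria". That section does not say which measure or cut-off is meant.

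**The concern.** The two parts of the CR-target ratio cover different periods. The numerator counts weeks at a restriction target, and the programme sets aside only 8 weeks for restriction. The denominator counts every week with enough diary entries, and diaries are required for 12. Each maintenance week that a woman records as instructed lowers her score, unless she was still eating at the restriction level during a phase meant to hold weight steady.

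What is at stake is the description of how well the CR diet was followed, which readers need to interpret either a positive or a null result. If the same categories feed per-protocol membership, the composition of that set is at stake as well. The article states the numerator, the denominator and the cut-offs, so this is a stated rule that gives a wrong result and not a detail left to a fuller document.

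**Working it through.** The article gives no worked adherence score, so there is no published figure to reproduce. The check applies the stated formula.

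**Inputs.** Restriction phase 8 weeks and maintenance phase 4 weeks (Overview). A week counts as recorded if it has at least 3 diary days; recording adherence = recorded weeks / 12; CR-target adherence = weeks on target / recorded weeks; cut-offs 80% and 60% (all from CR diet group).

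**Assumption for steps 1–3.** All 8 restriction weeks are recorded, and no maintenance week is at the restriction target.

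**Step 1. Effect of recording the maintenance weeks.** With *r* maintenance weeks recorded, CR-target adherence is 8/(8 + *r*) for a woman on target in all 8 restriction weeks, and 7/(8 + *r*) for one on target in 7. Recording adherence is (8 + *r*)/12 for both.

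| *r* | Recording adherence | CR-target, 8 of 8 | CR-target, 7 of 8 |
|---|---|---|---|
| 0 | 8/12 = 66.7% moderate | 8/8 = 100% high | 7/8 = 87.5% high |
| 1 | 9/12 = 75.0% moderate | 8/9 = 88.9% high | 7/9 = 77.8% moderate |
| 2 | 10/12 = 83.3% high | 8/10 = 80.0% high | 7/10 = 70.0% moderate |
| 3 | 11/12 = 91.7% high | 8/11 = 72.7% moderate | 7/11 = 63.6% moderate |
| 4 | 12/12 = 100% high | 8/12 = 66.7% moderate | 7/12 = 58.3% low |

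Dietary behaviour is the same all the way down each CR-target column. Only diary-keeping after week 8 changes, and better diary-keeping lowers the score.

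**Step 2. Being high on both measures.** High recording needs at least 0.80 × 12 = 9.6, so 10 weeks. With at most 8 weeks on target, high CR-target adherence needs at most 8/0.80 = 10 recorded weeks. Both hold only with exactly 10 recorded weeks: all 8 restriction weeks, all on target, plus 2 maintenance weeks. Recording the other two maintenance weeks, as instructed, moves her down a class.

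**Step 3. Full recorders, as written and restricted to weeks 1–8.**

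| Restriction weeks on target | As written (/12) | Weeks 1–8 only (/8) |
|---|---|---|
| 8 | 66.7% moderate | 100% high |
| 7 | 58.3% low | 87.5% high |
| 6 | 50.0% low | 75.0% moderate |
| 5 | 41.7% low | 62.5% moderate |

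For full recorders the written score is 8/12, or two thirds, of the score over the restriction phase.

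**Step 4. Relaxing the assumption.** Suppose all 12 weeks are recorded, all 8 restriction weeks are on target, and *m* maintenance weeks are also at the restriction target. The score is (8 + *m*)/12: 75.0% for *m* = 1, 83.3% for 2, 91.7% for 3 and 100% for 4. A full recorder therefore reaches high only by staying at the restriction level for at least half of the maintenance phase.

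**The case against.** The strongest reply is that the limit of 8 on the numerator is inferred. The article calls the whole intervention a 12-week CR diet, gives its energy goal no end date, and says of weeks 9–12 only that dietitian input stops. If the goal persists, 12/12 is attainable and the formula is coherent. This keeps the finding conditional on maintenance intake lying above the restriction target. It is hard to square, though, with a separate weight-maintenance phase after an 8-week restriction phase: an intake 30–50% below baseline expenditure holds weight steady only if expenditure has itself fallen by that much. If a 12-week target is what the sponsor intends, the Overview and the adherence definition still have to be reconciled.

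A reader might also draw three stronger conclusions, which the article does not support:

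- *That a compliant woman can never be classed as high.* She can, if she records no more than 2 maintenance weeks (step 1) or stays at the restriction target in enough of them (step 4).
- *That the per-protocol set is corrupted.* The article names neither the measure nor the cut-off for that set. If CR-target adherence were used, a rule of at least 80% would exclude the fully recording woman with 8 of 8 weeks on target. A rule of at least 60% would keep her and exclude the one with 7 of 8. Either result depends on a rule that is not stated.
- *That dividing by recorded weeks is itself an error because it rewards silence.* A woman with 3 recorded weeks, all on target, does score 3/3 = 100%, but her recording adherence is 3/12 = 25%, which is low and reported alongside. Judging target attainment on evaluable weeks and reporting evaluability separately is a legitimate design. Among women with the same number of recorded weeks, the score still rises with weeks on target.

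**Conclusion.** The point holds in a limited form. As written, CR-target adherence mixes an 8-week behaviour with a denominator of up to 12 weeks. It understates adherence for women who keep their diaries as instructed: 66.7% in place of 100% for 8 of 8 weeks on target, and 58.3% in place of 87.5% for 7 of 8. The second woman drops two classes. The result rests on two assumptions: that intake in the maintenance weeks lies above the restriction target, and that those weeks are recorded on at least 3 days each.

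The certain consequence, under those assumptions, is a misleading description of adherence in the CR arm. Distortion of the per-protocol set is possible but conditional on these categories being used there, and that analysis is only supportive. The primary intention-to-treat comparison of live birth does not use adherence and is untouched. The definition should be corrected, but it does not threaten the main result.

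**What to change.** Reconcile the Overview, the adherence definition and the description of the last four weeks. Specifically:

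1. Compute CR-target adherence over the restriction phase only: weeks on target in weeks 1–8, divided by recorded weeks in weeks 1–8. State how a woman with no recorded week in that period is handled, since the ratio is then undefined.
2. Keep recording adherence over 12 weeks as the paired measure, and report the two together.
3. Wherever CR adherence defines per-protocol membership, use the corrected measure together with recording adherence.
4. As an optional sensitivity version, divide by 8 and count unrecorded weeks as off target.

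If the sponsor means the restriction target to apply in weeks 9–12 as well, the text should say so and the description of the phases should be made to agree. That choice is the sponsor's, and none is proposed here.

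The cost is a sentence or two in the protocol or analysis plan and a changed derivation. The diary data are already being collected. The change should be made before the analysts are unblinded.

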#### Metformin group

After randomization, participants assigned to the metformin group will initially receive 1,000 mg per day (500 mg administered twice daily) for the first 3 days to enhance drug tolerability. Thereafter, the dosage will be escalated to the target level of 1,500 mg per day (500 mg administered three times daily) and maintained for the remainder of the 12-week intervention period. Although standard clinical practice often starts metformin at 500 mg/day and increases the dose weekly to minimize gastrointestinal side effects, this rapid escalation regimen was chosen based on prior clinical experience in this population. Participants will be closely monitored for gastrointestinal adverse effects, and dose adjustments or discontinuation will be considered when clinically necessary. They will receive routine clinical advice regarding dietary habits according to standard care and will not receive any materials or interventions related to the CR diet. However, no formal dietary measurements will be conducted during the 12 weeks of the intervention.

#### OI treatment

Prior to initiating OI therapy, a β-human chorionic gonadotropin (β-hCG) test must be performed to exclude pregnancy. Letrozole administration will begin on days 3–5 of the menstrual cycle, with an initial dosage of 5 mg/day. After five consecutive days of administration, transvaginal ultrasonography will be used to monitor follicular development. Based on ultrasonographic findings, human menopausal gonadotropin (HMG) 75 IU may be administered intramuscularly on a daily basis, with subsequent dosage adjustments determined by the follicular response. When the dominant follicle reaches a diameter of ≥14 mm, the monitoring frequency should be increased to alternate-day assessments, supplemented by endocrine profiling, and urinary luteinizing hormone (LH) surge detection. Once follicular maturation criteria are met (i.e., dominant follicle diameter of 1.8–2.0 cm), 10,000 IU of human chorionic gonadotropin (hCG) is administered intramuscularly to trigger ovulation, which typically occurs within 48 h post-injection. Following ovulation, oral progesterone capsules will be administered at a dose of 10 mg twice daily for luteal phase support. Treatment will continue until the serum β-hCG level is performed. If the pregnancy test is positive, dydrogesterone will be continued until clinical pregnancy is confirmed by ultrasonography. β-hCG levels will be measured 14 days later to confirm pregnancy. In cases of positive results, follow-up transvaginal ultrasonography will be performed 14 days thereafter to confirm clinical pregnancy. If the pregnancy test is negative, OI may be repeated in the next cycle, provided that normal baseline ultrasonographic findings are confirmed on days 3–5 of the subsequent menstrual cycle.

All participants will be strongly recommended to undergo hysterosalpingography (HSG) prior to treatment initiation to confirm bilateral tubal patency and to minimize potential bias between study groups. The decision to perform HSG will ultimately be made by the attending physician in consultation with the participant, considering individual clinical circumstances. Participants who fail to achieve pregnancy after 5 cycles should be referred for assisted reproductive technologies.

#### Safety monitoring

Adverse events will be actively monitored and documented throughout the 12-week intervention period in both treatment groups. In the metformin group, particular attention will be paid to gastrointestinal adverse effects, including nausea, vomiting, abdominal discomfort, and diarrhea. Participants who experience metformin intolerance will undergo clinical evaluation, and dose adjustment or discontinuation will be considered when necessary. In the CR diet group, potential diet-related adverse events or symptoms associated with energy restriction will be monitored by investigators and dietitians during follow-up, and the dietary intervention will be adjusted when clinically indicated. All adverse events will be documented with respect to their nature, severity, timing, management, outcome, and assessed relationship to the study intervention. Serious adverse events will be promptly evaluated by the principal investigator in collaboration with the Data Monitoring Committee (DMC), and appropriate clinical management and reporting procedures will be undertaken in accordance with the study protocol and applicable ethical requirements. The DMC will review relevant safety information and may recommend modification or discontinuation of the intervention or trial when warranted.

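### Adverse-event enquiry has a different symptom focus in each open-label arm, so any side-by-side report of gastrointestinal or energy-restriction symptoms may partly reflect what was asked and by whom

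*Protocol article*

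**What the plan says.** The Safety monitoring section of the protocol article starts from a common base: "Adverse events will be actively monitored and documented throughout the 12-week intervention period in both treatment groups". It also fixes common recording: "All adverse events will be documented with respect to their nature, severity, timing, management, outcome, and assessed relationship to the study intervention".

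On that base it adds two arm-specific instructions. For metformin: "In the metformin group, particular attention will be paid to gastrointestinal adverse effects, including nausea, vomiting, abdominal discomfort, and diarrhea". For the CR diet: "In the CR diet group, potential diet-related adverse events or symptoms associated with energy restriction will be monitored by investigators and dietitians during follow-up". The Metformin group section repeats the emphasis on close watching for gastrointestinal effects.

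Contact with staff is described only for the CR arm. In the first 8 weeks, "dietitians will provide individualized feedback to each participant twice a week via the app". In the last 4 weeks, "dietitians will discontinue active dietary intervention and no longer provided feedback on the CR protocol". Participants in this arm can also message dietitians through the app.

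Recruitment and randomization states that participants and the staff delivering the interventions cannot be blinded. The Introduction cites metformin's gastrointestinal effects among the limitations that call for safer and more effective alternatives.

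**The concern.** Symptoms that are asked about are generally recorded more often than symptoms left for the participant to mention. The article names gastrointestinal enquiry for metformin only and energy-restriction enquiry for CR only. In the CR arm, the dietitians who deliver the diet also watch for its harms. Unblinded staff who follow this text could probe each arm for different things.

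At stake is the tolerability contrast that readers will most likely draw. The Introduction makes gastrointestinal intolerance of metformin part of the case for an alternative, and that is the symptom group singled out in one arm. The limitations in the Discussion concede unequal attention as a difficulty in interpreting between-group differences, but do not connect it with how adverse events come to light. Unequal ascertainment during the 12 weeks cannot be repaired in the analysis.

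**Working it through.** **Step 1: the text side by side**

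| Feature | Metformin | CR diet | Same in both? |
|---|---|---|---|
| Active monitoring for 12 weeks | Yes | Yes | Yes |
| Attributes recorded per event | Common list | Common list | Yes |
| Symptoms singled out | Gastrointestinal | Diet-related and energy-restriction | No |
| Named observers | None named | Investigators and dietitians | No |
| Frequency of adverse-event enquiry | Not stated | Not stated | Cannot be judged |
| Dietary feedback contacts | None described | 2 per week × 8 weeks = 16 | No, but not described as adverse-event enquiry |

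The two shared rows say that both arms are watched and how an event is written down once known. They do not say that the same questions are asked in both arms.

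**Step 2: inputs for an illustration**

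The plan gives no adverse-event rate or capture rate, so no figure of its own on this point can be reproduced. The one input taken from it is the sample size: 406 randomised 1:1, or 406 / 2 = 203 per arm. Everything else is assumed:
- the true gastrointestinal rate is 20% in both arms;
- 90% of events are captured on metformin;
- 90%, 70% or 50% are captured on CR.

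**Step 3: recorded rates and risk ratios**

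Recorded rate = true rate × capture.
- Metformin: 0.20 × 0.90 = 0.18.
- CR at 90% capture: 0.18, risk ratio 1.00.
- CR at 70% capture: 0.20 × 0.70 = 0.14, risk ratio 0.18 / 0.14 = 1.29.
- CR at 50% capture: 0.20 × 0.50 = 0.10, risk ratio 0.18 / 0.10 = 1.80.

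The true rate cancels, so the apparent risk ratio is simply the ratio of the two capture rates.

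**Step 4: two-proportion z test, 203 per arm**

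z = (p1 − p2) / √(2 × p̄ × (1 − p̄) / 203), where p̄ is the mean of the two recorded rates.
- 70% capture: 0.04 / √(2 × 0.16 × 0.84 / 203) = 1.10, not significant.
- 50% capture: 0.08 / √(2 × 0.14 × 0.86 / 203) = 2.32, p = 0.02.

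**Step 5: range over the true rate**

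For true rates of 10% to 30% in both arms, with 90% capture on metformin:

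| Capture on CR | Risk ratio | Spurious risk difference | Chance of a falsely significant result |
|---|---|---|---|
| 70% | 1.29 | 2 to 6 points | 0.11 to 0.29 |
| 50% | 1.80 | 4 to 12 points | 0.35 to 0.85 |

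**The case against.** The strongest reply is that the common base already covers both arms. Active monitoring is required in each, and every event is recorded in the same way. Extra attention to a known risk is an emphasis on top of that and protects participants. This stands in part. It rules out saying that either symptom group is sought in one arm only, and it makes purely volunteered reporting on CR, which the 50% figure resembles, an extreme case. It does not remove the difference in focus, which the text states.

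Three stronger readings are tempting, and the documents support none of them.

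- **That adverse events are sought at a different contact frequency in each arm.** The twice-weekly contacts are feedback on diet, and no enquiry schedule is given for either arm. The contacts and the app messaging are at most an extra route by which events may surface on CR. That would raise CR counts, opposite in direction to the gastrointestinal focus.
- **That a planned safety comparison is biased.** The aims, outcome and statistical sections name no adverse-event outcome and no between-arm safety test. The issue arises only if rates are set side by side, and then the text supports only that they may be biased. Nor does it show that the Data Monitoring Committee will see a distorted comparison. It says only that the committee reviews safety information.
- **That no common symptom form exists.** An article may leave such a form to the full protocol. The point rests on the arm-specific wording that is printed, not on the missing form.

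**Conclusion.** The point holds in limited form. The article fixes a different symptom focus in each arm of an open-label trial, and in the CR arm gives part of the observing to the staff who deliver the diet. A between-arm difference in recorded gastrointestinal or energy-restriction symptoms could therefore partly be an artefact of enquiry.

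For gastrointestinal symptoms the stated focus would tend to raise metformin counts. For adverse events overall the net direction is not known. The size is not known either. The risk ratios of 1.29 and 1.8 rest wholly on assumed capture rates, and only the more extreme assumption gives a significant result at a true rate of 20%.

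The primary outcome and its analysis are unaffected. Arm-specific clinical monitoring is not itself an error.

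**What to change.** Keep the arm-specific clinical monitoring as it stands, because it leads into the evaluation of metformin intolerance and the adjustment of the diet for participants' safety. Add to Safety monitoring:

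- One symptom checklist with both gastrointestinal and energy-restriction items, asked in the same words of every participant at scheduled visits common to both arms. Weeks 4, 8 and 12 would serve if the schedule in Figure 2 applies to both arms. Only its legend is available here, so that needs confirming.
- A statement that any between-arm comparison of these symptoms uses the checklist data only.
- A separate listing of events learned through the app or dietitian contacts, with all serious events still reported whatever their source.

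If the full protocol already has such a form, a sentence saying so is enough. The cost is a few minutes per visit and slightly more data entry.
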